## BACKGROUND

### **Liquid volume and distribution of body water in adults and children**

Approximately 60% of an adult's body weight consists of water. In neonates under 1 year of age, the water content is close to 80% of body weight. After the first year of life, the water content decreases and by 9 years of age the water content is approximately the same as for adults. From a functional and clinical point of view, the water volume can be divided into two separate fluid compartments: 1) Intracellular fluid volume (ICV) and 2) extracellular fluid volume (ECV). Roughly two thirds of the body's water volume is located intracellular and the remaining third is distributed extracellular. The extracellular fluid volume is divided into two components; 1) intravascular fluid volume (= plasma volume represents 25% of ECV) and 2) extravascular fluid volume (= interstitial fluid volume, representing 75% of ECV or about 12-15% of the body weight of an adult). Compared to adults, the increased fluid volume per body weight is primarily localized as extracellular fluid in children. The reduction of body water, compared to total body weight during the first 10 years of life, is therefore primarily due to a reduction of extracellular water content. This amount constitutes approximately 40% of the body weight in neonates, and the relative amount decreases to 20% at puberty. Plasma volume represents about 5% of body weight in all age groups.

### **Fluid balance**

The regulation of the extracellular volume is of central importance to life and health. Failing regulation - as in hypovolemia - will at worst lead to hypovolemic shock and may be life threatening. On the other hand, gross hypervolemia - as with excessive infusion therapy - can lead to heart failure, pulmonary edema and potentially death. Robust mechanisms regulate and stabilize the extracellular volume, despite frequently occurring wide fluctuations in fluid losses and in salt and water intake. These regulatory mechanisms ensure, at all times, the best possible situation: Adequate salt and fluid balance, stabilization of the osmolality of interstitial fluid and adequate blood pressure. The regulation occurs as a result of the close interaction between pressure and volume receptors in the central circulation, kidneys, autonomic nervous system and endocrine systems (aldosterone and vasopressin).

Regulation of fluid transport between plasma and the interstitium takes place by communication between the fluid phases on a capillary level. Fluid transport over the capillaries requires a vessel wall that is permeable to water and crystalloids. Fluid exchange between plasma and interstitial fluid occurs by filtration due to hydrostatic pressure and absorption. The capillary wall is semi-permeable to plasma proteins, and most of these will not be pressure filtered, but be retained in the circulation. The pressure gradient for filtration and reabsorption of the capillary membrane is determined by the sum of the hydrostatic pressure, and the colloid osmotic pressure in the various sections of the capillary. Transcapillary transport of fluid ( $J_v$ ) is determined by the trans-capillary hydrostatic ( $P$ ) and colloid osmotic pressure ( $COP$ ) as described in equation (Starlings equation):

$$J_v = CFC ((P_c - P_i) - \sigma (COP_c - COP_i)) = CFC \cdot \Delta p = \text{Flow of lymph}$$

CFC is capillary filtration coefficient (water permeability),  $\sigma$  is the reflection coefficient for plasma proteins,  $\Delta p$  is the net pressure gradient across the capillaries and "c" and "i" are the capillary and interstitial fluid respectively. Normally, there is a net filtration of fluid across the capillary membrane, which will be balanced by a corresponding lymph drainage (flow of lymph) in order to achieve steady-state. Any change in the factors of Starlings equation, the hydrostatic pressures, the colloid osmotic pressures or flow of lymph, will affect transcapillary fluid transport and therefore both the plasma volume and the interstitial volume. It is important to note that the parameters of Starlings equation are not static, but changes in one parameter will often lead to compensatory changes in the other parameters. For example, an increase in capillary pressure ( $P_c$ ) or fall in  $COP_c$ , will lead to net transport of fluid from the plasma to the interstitium, resulting in increased interstitial fluid pressure ( $P_i$ ) and/or a decrease in  $COP_i$  (dilution). These changes were first postulated by Guyton and were called "edema preventing mechanism", i.e. mechanisms that counteract edema development. These mechanisms have subsequently been studied and mapped in several animal models, and has formed the basis for improved understanding of fluid balance and fluid therapy in various disease states.

### **Transcapillary Colloid Osmotic Pressure in adults and children**

Methods for sampling interstitial fluid and measurement of COP were established in the 1970s at the Department of Physiology, University of Bergen. Studies of the distribution of plasma proteins and fluid balance have been examined for various disease states with fluid retention, hypoproteinemia, hypothermia, kidney failure, increased venous pressure, pregnancy with edema, and in women with premenstrual syndrome. The results of these studies have been of great importance for the understanding of the pathophysiology of these conditions, and have been important in the choice of treatment. Normal range for  $COP_i$  for healthy adults is between 22 and 28 mmHg (mean 25 mmHg).

For newborn babies, COP in plasma would increase with increasing gestational age (extreme premature babies have lowest COP). COP in the plasma of healthy newborns are also low compared to adults, but COP in plasma increases with increasing age (especially in early childhood). The significance of the low COP values in plasma of healthy children and sick children (nephritic syndrome, traumatic bleeding, sepsis) is unknown because it is the relationship between COP in interstitial fluid and plasma ( $COP_p - COP_i$ ), which determines the water balance of the capillary membrane. The clinical value of plasma COP in children has therefore been limited, and fluid therapy has been based on extrapolation from data in adults. COP data from the interstitium in children, however, lacks entirely due to lack of methods to sample interstitial fluid. Recognition of COP in interstitial fluid in healthy children is nevertheless important to address because this knowledge will benefit fluid therapy in critically ill children. Today, normal values for COP from interstitial fluid in healthy children do not exist, and thus the use of COP plasma levels in critically ill children and premature is of limited value. Establishing normal values for COP in interstitial fluid in healthy children is therefore important to understand fluid therapy in critically ill children.

## **SIGNIFICANCE**

Analysis of protein content and COP in interstitial fluid provides valuable information regarding fluid balance. Knowledge of fluid balance in children is essential in most anesthetic, surgical and pediatric work areas. Improved understanding of fluid balance increases our ability to provide adequate fluid therapy, or at least avoid inadequate or excessive fluid therapy. Adequate fluid therapy is often critical to a patient's wellbeing and is in some situations essential for survival. Albumin accounts for 80% COP in the plasma of healthy individuals, but only 17% in critically ill adults. Similar data are lacking in children. Albumin solutions (colloids) are often used to correct hypoalbuminemia in adult intensive care units (ICU), patients without evidence of adverse effect on mortality. Similar data for children are missing completely and knowledge of normal values for COP in plasma and in the interstitium will have great significance for the choice of treatment for fluid substitution and hypoproteinemia states (nephrotic syndrome, malignant disease, etc.).

## **TIME PERIOD**

The study will begin on 1 September 2006 and we expect to finish the study, 31 December 2007. If the aim of 100 patients is met before, the study will be completed earlier.

## **OBJECTIVES AND HYPOTHESIS**

The project aims to establish methods for sampling and measurement of colloid osmotic pressure (COPi) in tissue fluid in children. The primary objective of this study is to find normal values of COPi in healthy children aged 2-10 years. There is currently no data on COPi either in healthy or sick children.

The project has five main hypotheses:

- 1) It is possible to sample tissue fluid by the wick method and measure COPi (and protein fractions) in children aged 2-10 years.
- 2) The time that equilibrium is achieved by the wick method is similar to that in adults (60 min.) (with the assumption that adult values of COP are reliable).
- 3) COPi is age-dependent and correlates well with the age-specific values for COP in plasma.
- 4) COPi ankle is correlated to the height, and difference between COPi in ankle and thorax will increase with increasing height (hydrostatic pressure in the lower limbs is dependent on gravitational forces and, thus, increased height may increase filtration of proteins in the subcutaneous tissue of the ankle).
- 5) The relationship between albumin and total protein (albumin / total protein ratio) in tissue fluid increases with increasing age (verify the clinical observations during fluid therapy and animal experimental data that indicate increased capillary-bed leakage with decreasing age).

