## **PATIENTS**

Population will be recruited from "healthy" patients admitted to elective surgery (tonsillectomies, tympanic membrane paracentesis, adenotomy) at the Department of Ear-Nose-Throat (ENT), Haukeland University Hospital. The hospital treats annually about 500-600 children (10-15 per week for 40 weeks per year) with these diagnoses. The majority of patients will be in the age group 2-5 years. Most patients will be under general anesthesia between 60 and 90 minutes in relation to the surgical procedure.

**Protocol:** There will be drawn one venous blood sample (1-2 ml from i.v. line) for determination of plasma protein and the COP of plasma. Two nylon "wicks" will be inserted subcutaneously (ankle + thorax) for determination of protein content and the COP in interstitial fluid (2-5 µl. per wick). Both procedures will be conducted after the child is under general anesthesia (combined fentanyl-propofol anesthesia) and the wicks will be removed after 60 (-90) minutes before the child is extubated/awakened from anesthesia. After removal of the wick a traditional band-aid will cover the site of insertion. All participants will be given analgesia postoperatively according to current guidelines at the ENT clinic. During the procedure and through the postoperative course, blood pressure, oxygen saturation, heart rate, respiratory rate and amount of bleeding will be monitored. The project will have no impact on the type of intervention, duration of anesthesia or post-operative follow-up.

**Inclusion criteria:** Informed consent from parents  
Age 2 - 10 years

**Exclusion criteria:** Syndromes (ex. Down Syndrome, Turner)  
Chronic diseases (ex Cardiovascular and Kidney Diseases)  
Bleeding from surgical procedure more than 10% of total blood volume during surgery

Number of patients to be included will be a total of 100 children (10 in each age group (2-3, 3-4, 4-5, 5-6, 6-7, 7-8, 8-9, 9-10 years) n = 80. In 20 children where general anesthesia duration is expected to last > 90 minutes, both wicks will be inserted subcutaneously in the ankle where one wick will be removed after 60 minutes and the second after 90 minutes (time for equilibrium for wick method in children)

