## **METHODS**

Protein content and COP in plasma will be determined from the venous blood sample. Interstitial fluid will be collected by sewing two wicks in to the subcutaneous tissue (Figure 1a). The wicks are about 2 mm thick and consist of about 300 nylon fibers, which are sterilized by gamma radiation. Wicks will be inserted above the right ankle and right lateral hemithorax after the patient is put under general anesthesia, and after the skin is washed with 0.5% chlorhexidine. Under sterile conditions, by means of the needle the 30-40 mm of the wick will be stitched subcutaneously under the skin (Figure 1a). The wick is trimmed at both ends leaving about 10 mm of wick outside the skin, covered with a sterile plastic film. The wick will remain under the skin for one hour (or 90 minutes in 20 patients) before it is removed and placed in a centrifuge tube with mineral oil (Figure 1b). The tube is centrifuged, and the harvested interstitial fluid is contained at the bottom of the tube. Tube containing interstitial fluid and mineral oil is frozen for further analyzes (Figure 1c). Using this method, it is possible to extract 2-5 $\mu$ l fluid per week, and 1-2  $\mu$ l will be used for the measurement of the COP using a colloid osmometer (Figure 1d) designed for small sample volumes (1-2  $\mu$ l). The remaining volume will be analyzed for protein content and distribution of macromolecules by means of an HPLC system.

[figure not shown]

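### Hypothesis 5 infers capillary leakage from the albumin/total protein ratio in tissue fluid alone; an age change in plasma composition, if there is one, could mimic or mask the effect

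*Protocol*

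**What the plan says.** The Protocol, under Objectives and Hypothesis, lists five main hypotheses. The fifth fixes a measure: "The relationship between albumin and total protein (albumin / total protein ratio) in tissue fluid increases with increasing age". The parenthesis after it fixes what the measure is for, namely to "verify the clinical observations during fluid therapy and animal experimental data that indicate increased capillary-bed leakage with decreasing age". No plasma quantity enters. Hypothesis 3 in the same list does relate a tissue value (interstitial COP) to its plasma counterpart.

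On measurements, the Patients section has one venous sample per child, "for determination of plasma protein and the COP of plasma". The Methods section repeats this: "Protein content and COP in plasma will be determined from the venous blood sample". Neither place names plasma albumin. Fractionation is described for the wick fluid left after the COP reading: "The remaining volume will be analyzed for protein content and distribution of macromolecules by means of an HPLC system".

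The Statistics section gives no effect size, SD or significance level and calls the study essentially descriptive.

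**The concern.** Protein in interstitial fluid comes from plasma across a capillary wall that the Protocol's background describes as semi-permeable to plasma proteins. The albumin share found in the wick therefore has two sources: the albumin share in the plasma being filtered, and how selectively the wall passes albumin compared with other proteins. Hypothesis 5 attributes an age trend in this share to the second source without holding the first fixed.

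If the plasma ratio rises with age, the tissue ratio rises too, and the hypothesis looks confirmed with no change in permeability. If the plasma ratio falls with age, a real permeability change can be hidden. The Protocol makes the parallel argument itself for COP: its section on transcapillary COP says that the plasma value alone has limited use, because the relation between plasma and interstitium governs water balance. At stake is the mechanistic conclusion of hypothesis 5, not the normal values of interstitial COP.

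**Working it through.** **Inputs from the Protocol.** The measure and its purpose (hypothesis 5). Sample (Patients section): 8 age groups × 10 = 80, plus 20 in the 60/90-minute group = 100, which reproduces the stated total. There is no effect or power figure for hypothesis 5 to reproduce.

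**Assumed inputs (the Protocol gives none).** Plasma albumin fraction f between 0.55 and 0.60; tissue/plasma concentration ratios kA for albumin and kG for other protein; the SDs named below.

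**Step 1: what the tissue ratio contains.** The tissue albumin fraction is

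t = kA·f / [kA·f + kG·(1 − f)].

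With kA and kG fixed (permeability constant) and f moving from 0.55 to 0.60:

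| kA / kG | t at f = 0.55 | t at f = 0.60 | change in t | tissue odds / plasma odds |
|---|---|---|---|---|
| 0.5 / 0.3 | 0.671 | 0.714 | +0.044 | 1.667 at both |
| 0.6 / 0.4 | 0.647 | 0.692 | +0.045 | 1.5 at both |
| 0.5 / 0.4 | 0.604 | 0.652 | +0.048 | 1.25 at both |

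First row: 0.275/(0.275 + 0.135) = 0.671 and 0.300/(0.300 + 0.120) = 0.714. A plasma fall from 0.60 to 0.55 gives the same changes with a minus sign. If f does not move, t does not move.

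**Step 2: which plasma reference removes this.** From the formula, t/(1 − t) = (kA/kG) · f/(1 − f). Tissue odds divided by plasma odds equal kA/kG whatever f is, as the last column shows. The simple quotient t/f does not have this property. In the first row it goes from 0.671/0.55 = 1.22 to 0.714/0.60 = 1.19. On the log scale the raw ratio moves by +0.063 and the quotient by −0.024, so about 38% of the bias (0.024/0.063) remains, with its sign reversed.

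**Step 3: consequence for a slope on age.** Simulation with 80 children (10 in each of 8 age groups), a linear slope on age, a two-sided 5% test and 3000 runs. Mean f is 0.60 with between-child SD 0.03; kA/kG = 0.5/0.3; the SD of the tissue-minus-plasma log odds is 0.15 or 0.25; plasma is measured without error. Permeability does not change with age.

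| plasma change, age 2 to 10 | tissue ratio alone significant | log tissue odds minus log plasma odds significant |
|---|---|---|
| 0 | 5% | 5% |
| 0.02 | 11–19% | 5% |
| 0.04 | 33–58% | 6% |
| 0.06 | 61–91% | 5% |

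Masking (SD 0.15): with a true permeability change of +0.2 in log odds and a plasma change of −0.05, the tissue ratio alone detects the trend in 5% of runs and the plasma-referenced measure in 93%. With no plasma change the figures are 73% and 92%.

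**Step 4: a cruder cross-check.** Suppose the plasma-driven drift in the tissue ratio itself is d over the age range and the between-child SD is 0.05. The trend SD is d/√12 and r = trend SD / √(trend SD² + 0.05²). For d = 0.03, 0.05 and 0.07, r = 0.17, 0.28 and 0.38. With n = 80, Fisher's z gives significance at 5% in 33%, 71% and 93% of studies. At d = 0, r is 0 and the rate is the nominal 5%.

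**The case against.** The strongest reply is that nothing in the Protocol shows a plasma trend to correct for. The background says that plasma COP rises with age, and the Significance section says "Albumin accounts for 80% COP in the plasma of healthy individuals". A reader might infer from these that the plasma albumin/total protein ratio also rises and that hypothesis 5 is therefore biased towards confirmation. The documents do not support that. COP can rise while albumin and total protein rise in proportion, which leaves the ratio flat. The COP statement comes in a paragraph that starts from newborns and gives no figure for ages 2 to 10. The 80% figure is for healthy individuals, and the Protocol adds that comparable data in children are lacking. This part of the objection stands: the bias is possible, in either direction, and its size is not known.

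A reader might also take the child's plasma ratio to be already in the data. The text commits to plasma protein and plasma COP without naming albumin, so the ratio is obtainable from the sample but not promised. That stands too.

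Third, the study is labelled descriptive, and an analysis plan could add an adjustment. The label protects the descriptive half of hypothesis 5, which can be answered as written. It does not protect the parenthesis, which names a mechanism to be verified from a tissue-only measure. A later plan can adjust for plasma albumin only if plasma albumin has been measured.

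**Conclusion.** The concern holds for the leakage reading only. The tissue albumin/total protein ratio cannot by itself distinguish an age change in capillary selectivity from an age change in plasma composition, yet hypothesis 5 attaches the first meaning to it. That the tissue ratio does or does not rise with age remains a valid descriptive result.

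The figures above are illustrations under assumed plasma drifts, concentration ratios and SDs, and they apply a 5% test that the Protocol does not specify. They show that a plasma change of a few hundredths could produce or hide a trend with 80 children. They do not show that this will happen. With no plasma trend there is no bias, and that remains a possibility.

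This is a cheap improvement. It concerns one of five hypotheses and leaves the primary objective, normal values of interstitial COP, untouched.

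**What to change.** 1. In the Methods section, state that albumin and total protein (or the same HPLC fractions) are determined in each child's plasma sample, by the same method as in the wick fluid.
2. In hypothesis 5, separate description from mechanism. Keep the raw tissue ratio by age as the descriptive result.
3. Test the leakage reading in one of two ways, chosen in advance:
   - regress the tissue ratio on age with the child's own plasma ratio as a covariate; or
   - regress on age the log of tissue odds over plasma odds. This is the same as the log of the tissue/plasma concentration ratio of albumin over that of non-albumin protein.
4. Do not use the log of tissue ratio over plasma ratio as the main endpoint. It fixes the plasma coefficient at 1, so it is not interchangeable with the covariate model, and in the example above it leaves a trend of opposite sign.

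Cost: a small plasma assay on the 1–2 ml sample already drawn, plus a few lines of text. No further procedure on the child is needed. Assay error in the plasma ratio would make either adjustment less complete or less precise, which is one more reason to use the same method for both fluids.

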## **PATIENTS**

Population will be recruited from "healthy" patients admitted to elective surgery (tonsillectomies, tympanic membrane paracentesis, adenotomy) at the Department of Ear-Nose-Throat (ENT), Haukeland University Hospital. The hospital treats annually about 500-600 children (10-15 per week for 40 weeks per year) with these diagnoses. The majority of patients will be in the age group 2-5 years. Most patients will be under general anesthesia between 60 and 90 minutes in relation to the surgical procedure.

**Protocol:** There will be drawn one venous blood sample (1-2 ml from i.v. line) for determination of plasma protein and the COP of plasma. Two nylon "wicks" will be inserted subcutaneously (ankle + thorax) for determination of protein content and the COP in interstitial fluid (2-5 µl. per wick). Both procedures will be conducted after the child is under general anesthesia (combined fentanyl-propofol anesthesia) and the wicks will be removed after 60 (-90) minutes before the child is extubated/awakened from anesthesia. After removal of the wick a traditional band-aid will cover the site of insertion. All participants will be given analgesia postoperatively according to current guidelines at the ENT clinic. During the procedure and through the postoperative course, blood pressure, oxygen saturation, heart rate, respiratory rate and amount of bleeding will be monitored. The project will have no impact on the type of intervention, duration of anesthesia or post-operative follow-up.

**Inclusion criteria:** Informed consent from parents  
Age 2 - 10 years

**Exclusion criteria:** Syndromes (ex. Down Syndrome, Turner)  
Chronic diseases (ex Cardiovascular and Kidney Diseases)  
Bleeding from surgical procedure more than 10% of total blood volume during surgery

Number of patients to be included will be a total of 100 children (10 in each age group (2-3, 3-4, 4-5, 5-6, 6-7, 7-8, 8-9, 9-10 years) n = 80. In 20 children where general anesthesia duration is expected to last > 90 minutes, both wicks will be inserted subcutaneously in the ankle where one wick will be removed after 60 minutes and the second after 90 minutes (time for equilibrium for wick method in children)

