## STATISTICS

Power calculation is not applicable because the study is essentially purely descriptive. Data will be processed by the usual descriptive statistical methods.

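### Descriptive statistics on 10 children per year of age are a weak route to normal limits of COPi; regression on exact age would use the same children better

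*Protocol*

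**What the plan says.** Under Objectives and Hypothesis, the Protocol states: "The primary objective of this study is to find normal values of COPi in healthy children aged 2-10 years". Hypothesis 3 in the same section expects that "COPi is age-dependent and correlates well with the age-specific values for COP in plasma".

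Under Patients, the sample is set out as "Number of patients to be included will be a total of 100 children". The main part is "10 in each age group (2-3, 3-4, 4-5, 5-6, 6-7, 7-8, 8-9, 9-10 years) n = 80". The rest is the timing sub-study: "In 20 children where general anesthesia duration is expected to last > 90 minutes, both wicks will be inserted subcutaneously in the ankle", with one wick removed at 60 and the other at 90 minutes.

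The whole Statistics section is two sentences: "Power calculation is not applicable because the study is essentially purely descriptive" and "Data will be processed by the usual descriptive statistical methods".

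The Background subsection on transcapillary colloid osmotic pressure shows what the Protocol means by a normal value. It gives the adult COPi as a range with a mean: "for healthy adults is between 22 and 28 mmHg (mean 25 mmHg"). Reading the primary objective as a search for reference limits, and not only for means, is therefore fair.

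**The concern.** The objective needs limits, the outcome is expected to change with age, and the stated method is descriptive summary. That method leads naturally to one of two results, and neither serves the objective well.

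- Summaries by year of age rest on 10 children each. Ten values say little about the 2.5th and 97.5th centiles, so limits would shift between neighbouring years largely by chance.
- Summaries over all ages ignore the age trend that Hypothesis 3 expects. Limits would be off-centre for the youngest and the oldest children.

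The Protocol says that no COPi data exist for children and hopes that these values will inform fluid therapy in critically ill children. First-ever limits that are noisy or age-biased could mislead their users.

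**Working it through.** **The plan's own figure.** 8 age groups × 10 = 80, and 80 + 20 = 100. Both reproduce. The Protocol gives no precision calculation, so there is none to check.

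**Inputs.** Group size 10, main sample 80 and total 100 come from Patients. The Protocol gives no SD of COPi in children, so results are in SD units. Assumptions: normal residuals, ages spread evenly over 2 to 10, and a usable sample from every child.

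**Formula.** For a limit of the form mean ± 1.96 SD:

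SE = SD × √(h + 1.96² / (2 × df))

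Here h is the leverage at the age in question (1/n for a simple mean) and df is the residual degrees of freedom. The 95% half-width is 1.96 × SE.

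**One age group of 10.**
- SE = √(1/10 + 3.8416/18) = 0.560 SD, so the half-width is 1.10 SD.
- Without a normality assumption, the lowest-to-highest range covers on average (10 − 1)/(10 + 1) = 82% of children. It covers at least 95% with probability 1 − (10 × 0.95⁹ − 9 × 0.95¹⁰) = 8.6%.
- In simulated normal samples, mean ± 1.96 SD from 10 children truly covered between 69% and 99% of children (central 95% of samples). With 80 children, ignoring age, it covered 90% to 98%.

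**All ages pooled.** Take, as an illustration only, a linear trend of D within-age SDs from age 2 to age 10. The pooled SD is √(1 + D²/12), and the mean at age 2 lies D/2 below the centre.
- D = 1: pooled SD 1.041, lower limit −2.04, mean at age 2 −0.5. The proportion of healthy two-year-olds below the limit is Φ(−1.54), about 6%.
- D = 2: pooled SD 1.155, lower limit −2.26, mean at age 2 −1. The proportion is Φ(−1.26), about 10%.

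The intended figure is 2.5%.

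**Regression on exact age, same 80 children.**

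| Model | Half-width at age 6 | Half-width at age 2 |
|---|---|---|
| Linear mean, constant SD | 1.96 × √(1/80 + 3.8416/156) = 0.38 SD | 1.96 × √(4/80 + 3.8416/156) = 0.54 SD |
| Quadratic mean, constant SD | 0.45 SD | 0.73 SD |
| Linear mean, log-linear SD | 0.37 SD | 0.75 SD |

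Against 1.10 SD, the gain runs from 1.10/0.38 = 2.9-fold at age 6 to 1.10/0.75 = 1.5-fold at age 2.

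**Ankle at 60 minutes with all 100 children** (linear mean, constant SD): 1.96 × √(1/100 + 3.8416/196) = 0.34 SD at age 6, and 1.96 × √(4/100 + 3.8416/196) = 0.48 SD at age 2. This also assumes that the 20 sub-study children are evenly spread in age, which the Protocol does not state.

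**In mmHg, by assumption.** If the adult range of 22 to 28 is read as mean ± 2 SD, the SD is 1.5. Read as ± 1 SD, it is 3. The half-width for a group of 10 is then 1.10 × 1.5 = 1.65 or 1.10 × 3 = 3.3 mmHg. The linear model gives 0.57 to 0.80 mmHg with SD 1.5, and about 1.1 to 1.6 mmHg with SD 3.

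**The case against.** A reader might infer that the Protocol plans separate limits in each year of age, or that the quota of 10 is itself the error. The document supports neither. The age groups appear only in the recruitment numbers, and nothing there or under Statistics commits to limits by group. Hypotheses 3 to 5 treat age and height as graded correlates, which points away from a group-only analysis. An even spread over age is also what a regression needs. This part of the objection stands, and the quota should stay.

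A statistical analysis plan that is not at hand may name the reference method, and details such as the form of the age curve belong there. That lowers the severity. It does not remove the point, because the Statistics section does not defer to a later plan: it states a method and sets aside any sample-size reasoning on the ground that the study is descriptive.

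A reader might also infer that regression settles the matter at every age. It does not. The 0.38 and 0.54 SD figures are the favourable case. The Background says that plasma COP rises with age especially in early childhood, and Hypothesis 3 ties COPi to plasma COP, so curvature at the youngest ages is plausible. There the advantage shrinks to about 1.5-fold.

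Finally, the 20 sub-study children are selected for a longer expected anaesthesia and carry two wicks at the ankle. Their comparability with the other 80 cannot be taken for granted.

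**Conclusion.** The concern holds as a mismatch between the primary objective and the stated method. Descriptive summaries by year of age would give limits with a 95% half-width of about 1.10 SD. Pooled summaries would be biased at the age extremes if Hypothesis 3 is right. Regression on exact age in the same children narrows the limits by about 1.5- to 2.9-fold and removes the pooling bias, provided that the age curve is adequate and the residuals are close to normal.

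The size in SD units depends on those model assumptions. The size in mmHg depends also on an assumed SD taken from adults. Severity is moderate: the data to be collected support the better analysis, and nothing is lost if the method is fixed before the data are analysed.

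**What to change.** Keep the quota of 10 per year of age, and say that it is for recruitment only. In the Statistics section, state that:

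- the primary result is 95% reference limits of COPi, separately for ankle and thorax, from regression of COPi on exact age;
- curvature of the mean, age-dependence of the SD and the distribution of the residuals will be checked;
- the limits will be reported with 95% confidence intervals across the age range, so that looser precision near ages 2 and 10 is visible;
- summaries by age group are descriptive only;
- the 60-minute ankle values of the 20 sub-study children may join the ankle curve after a check that they are comparable with the rest. The thorax curve rests on the 80, because the sub-study children have no thorax wick.

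The cost is a change of analysis wording, with no extra children, wicks or blood samples. The downside is that a smooth age trend and a distributional form must be assumed and checked.
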